## Methods

### Data Source

The Canadian Primary Care Sentinel Surveillance Network (CPCSSN [40]) is a multidisease electronic medical record (EMR) research and surveillance data repository that securely collects deidentified health information from EMRs of participating primary care clinicians (eg, family physicians and nurse practitioners) who are referred to as “sentinels.” CPCSSN currently brings together 13 primary care research networks for the purposes of research, disease surveillance, and quality improvement, with more networks due to join in the near future. Every 6 months, CPCSSN acquires deidentified patient-level clinical data from primary care EMR systems held by 1583 primary care providers across Canada, with approximately 200 patient encounters per month per physician [20]. CPCSSN acquires most of the data fields in Canadian primary care EMRs with the exceptions of portable document format such as imaging data and the narrative “Subjective, Objective, Assessment, and Planning” notes. The acquired data are processed into a standard format and are made available for surveillance and research [41]. The relative frequency, longitudinal format, and comprehensiveness of CPCSSN data are ideal for the study of changes in practice, through time, in response to significant environmental imperatives, such as public health or research initiatives [41]. Numerous case definition validation studies have been completed [42-44], and the data have also been used to evaluate patterns and quality of health care [19,45].

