### Study Design

This protocol was designed using the RECORD (REporting of studies Conducted using Observational Routinely collected Data) statement [46]. We will conduct a retrospective closed cohort study with a single group using a pre-post design. We will examine prevention and management activities for exemplar conditions on the basis of having a validated CPCSSN case definition [47,48] (ie, diabetes and heart failure), having substantial prevalence in primary care, and either having high morbidity or being risk factors for morbidity if not well managed. Patient-level data extracted from the CPCSSN repository between 2018 and 2022 will be used to investigate changes in rates of presentation and clinical management of various chronic diseases before, and through the phases of, the pandemic.

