### Study Population

The study population is all patients who were 18 years and older in 2018, and some analyses will focus on subgroups of patients with specific chronic conditions. We will use the 2-year contact population as recommended previously for defining practice populations for primary care [49]. This method uses contacts within encounter, medication, and billing-related data tables, and has been used previously with CPCSSN data to produce national chronic disease estimates [50]. This method will be used in the period from March 13, 2018, to March 13 2020. We will use this population rather than the full CPCSSN patient population data (dating back more than 2 decades for some networks) to limit the size of the data set, while maintaining the patient population that is likely to have a relationship with a primary care practice during the study period. Although this approach may exclude patients who are younger, healthier, and less likely to seek primary care compared with patients with chronic conditions, we do not expect this to have a major impact on findings because this study focuses on the age group where chronic condition prevalence begins to increase and where screening guidelines apply (eg, diabetes). Therefore, this age group is more likely to see a primary care physician regularly.

People who died during the study period will be included up to the point of death using the death date if captured or the presence of a deceased status with date estimated from the most recent contact in CPCSSN data. Patients who were older than 105 years at the start of the COVID-19 pandemic will be excluded as a possible data error.

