### Variables of Interest

#### Primary Exposure

The primary exposure is the start of the pandemic in March 13, 2020. This date was selected as it marks the beginning of Canadian provincial governments responding to the formal declaration of the pandemic by the World Health Organization on March 11, 2020, by enforcing sweeping public health and safety measures. The prepandemic time frame used is defined as June 22, 2018, through March 12, 2020. The pandemic time frame used in this study runs from March 13, 2020, through December 31, 2022. In addition to comparison between these 2 periods, 30-day interval rates will also be calculated for selected outcomes and indicators where possible.

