^q^NRT: nicotine replacement therapy.

*Access* to the practice will be measured as the overall number of encounters.

*Comprehensiveness* refers to primary care addressing “all problems in the population (with short-term referral as needed), except those that are too unusual (generally a frequency of less than 1 or 2 per thousand in the population served) for the primary care practitioner or team to treat competently” [1]. As indicators of comprehensiveness, we will measure number of different diagnoses addressed per patient per year, proportion of patients’ chronic conditions addressed at least once a year, number of pneumococcal vaccines and influenza vaccines in patients 65 years or older, and number of prescriptions for nicotine replacement therapy

*Appropriateness* will be examined in 2 ways: laboratory tests that are indicated for monitoring of chronic conditions but may be ordered more frequently than necessary (eg, hemoglobin A_1c_ in diabetics) and laboratory tests that are frequently ordered routinely (or for screening purposes) but may be overused in certain populations, including thyroid function tests, vitamin D, albumin-to-creatinine ratio, and lipid panel testing [53]. We hypothesize that some of these tests, while indicated at a base frequency, may be commonly overused; thus, their frequency may have declined during the pandemic.

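### Dating an unrecorded death to the last contact lets the measured outcome end observation: a small bias in rate ratios, a larger one in proportion indicators where mortality is high

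*Protocol article*

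**What the plan says.** Study Population sets the rule in two steps. A recorded date comes first: "People who died during the study period will be included up to the point of death using the death date if captured". Failing that, the plan uses "the presence of a deceased status with date estimated from the most recent contact in CPCSSN data".

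Four other statements bear on it:

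- **Design.** "We will conduct a retrospective closed cohort study with a single group using a pre-post design" (Study Design).
- **Entry.** Patients enter through the 2-year contact population: "This method will be used in the period from March 13, 2018, to March 13 2020". No contact is required after that.
- **Meaning of contact.** For cohort entry, "This method uses contacts within encounter, medication, and billing-related data tables". The article does not define contact separately for the death rule; I assume it is the same.
- **Outcome.** Access "will be measured as the overall number of encounters". Table 1 adds many proportions, several over 6 or 12 months.

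The one sensitivity analysis described concerns representativeness. Strengths and Limitations mentions incomplete capture of information in general, but not this rule.

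**The concern.** Censoring at death is sound when the date of death has nothing to do with the outcome. Here, for undated decedents, the date is the last contact. What is deleted is always the stretch without contact before death, and that stretch is longer when contact is sparser. A patient who lost care at the onset of the pandemic and later died undated is treated as having died before the pandemic began.

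Two kinds of result are exposed. Person-time rates lose denominator but no events, so they rise. Proportions lose people who would have counted as not receiving care. Both effects are greatest where mortality is high, as among older patients, for whom the Conclusions section hopes either to show gaps or to reassure. This is a stated rule, not a detail left to a fuller document.

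**Working it through.** The plan gives no figure on death dating to reproduce; its sample size calculation does not bear on this point. The undated share, mortality and contact rates below are assumptions.

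**1. Date arithmetic (undated deaths).** The pandemic period starts on March 13, 2020.

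- Last contact March 10, 2020, death March 10, 2021: 362 pandemic days without care become 0, and the patient leaves the pandemic period.
- Last contact June 1, 2020, death June 1, 2021: 445 pandemic days become 80, so one contact in 445 days is analysed as one in 80.

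**2. Pre-post rate ratio.** "The prepandemic time frame used is defined as June 22, 2018, through March 12, 2020": 630 days. The pandemic period to December 31, 2022 is 1,024 days, or 2.80 years. The rule leaves encounters intact and trims person-time in both periods, so

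analysed ratio = true ratio × (1 − share of prepandemic time lost) / (1 − share of pandemic time lost).

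The shares come from simulation (1,000,000 patients, Poisson contacts at 4 per year before the pandemic, exponential death). In the least favourable pattern, 25% of patients lose all contact at onset and the rest are unchanged. With all deaths undated:

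| Yearly mortality | Prepandemic time lost | Pandemic time lost | True ratio | Analysed ratio |
|---|---|---|---|---|
| 1.5% | 0.511% | 0.778% | 0.750 | 0.750 × 0.99489/0.99222 = 0.752 |
| 10% | 3.163% | 5.009% | 0.751 | 0.751 × 0.96837/0.94991 = 0.766 |

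At 10% mortality and 50% undated, 0.751 becomes 0.758; at 10% undated, 0.752. If instead every patient's rate falls by a quarter, 0.750 becomes 0.753 with all deaths undated. A halving from 6 to 3 contacts per year, with equal rates across patients, moves 0.500 to 0.506. With no true change, at 10% mortality and half of deaths undated, the ratio is 0.995 to 0.999.

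**3. A proportion: any contact in the pandemic period.** Assume 10% yearly mortality, 25% losing all contact, and 75% continuing at 4 per year.

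- Share dying in 2.80 years: 1 − exp(−0.28) = 0.2445.
- Among those still in contact, share dying before a first pandemic contact: 0.1/(0.1 + 4) = 0.0244.
- True proportion with any contact: 0.75 × (1 − 0.0244) = 0.7317.
- Decedents without pandemic contact: 0.25 × 0.2445 + 0.75 × 0.0244 = 0.0794.
- Analysed proportion with share u undated: 0.7317/(1 − 0.0794u), which is 73.8%, 76.2% and 79.5% at u = 10%, 50% and 100%.

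Equal contact rates are unrealistic. I repeated this by simulation with rates varying between patients (gamma, shape 2, mean 4 per year) and the 2-year entry rule applied:

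| Undated | Prepandemic | Pandemic | Difference (points) |
|---|---|---|---|
| True dates | 97.4% | 71.4% | −26.0 |
| 10% | 97.6% | 72.0% | −25.5 |
| 50% | 98.3% | 74.7% | −23.5 |
| 100% | 99.2% | 78.5% | −20.7 |

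The prepandemic proportion moves little because entry already requires a contact, so there is less to offset the pandemic error than in the rate ratio. At 1.5% mortality with equal contact rates, the pandemic proportion moves only from 74.7% to 75.7% with all deaths undated.

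**4. Shorter follow-up.** Future Analyses says data then ran to December 2021: 659 days, or 1.80 years. The closed form then gives 73.2% becoming 73.6%, 75.4% and 77.8%.

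**The case against.** **The bias largely cancels in rates.** This stands. A reader might infer that the rule hides most of the pandemic decline. Among undated decedents the distortion is indeed large: in the simulations 12% to 33% of those dying in the pandemic fall to zero pandemic time, and their contact ratio moves from 0.71–0.76 to 0.91–1.15. But the protocol does not report that stratum, and its ratio also rises with no true change (0.999 to 1.184 at 4 contacts per year). A reader might also quote the inflation of the pandemic rate alone, 1/0.94991, or about 5%, in the worst case above. The study estimates a pre-post contrast, where the prepandemic rate is inflated too (1/0.96837, about 3%), leaving about 2%.

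**The access outcome is a count.** This stands for a raw total: deleting time without contacts deletes no encounters. It does not cover the rates promised in the Abstract and Primary Exposure, or the proportions in Table 1. The article does not give their denominators, so the effect on them is conditional on the plain reading that a patient dated as dead is no longer counted.

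**Contact is wider than a visit.** This stands if the cohort definition applies: a prescription or billing entry would postpone the estimated death and shorten the deleted gap. It does not remove the gap.

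**The most exposed groups.** A reader might infer that the Conclusions section names heart failure or the sickest patients. It names those who are older or of lower socioeconomic status. Heart failure matters here as an exemplar condition, with mortality assumed, not documented.

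**Extraction dates may not rescue the death date.** This stands too. Data Source says "Every 6 months, CPCSSN acquires deidentified patient-level clinical data from primary care EMR systems", but not that past extractions are kept or that deceased status is entered promptly. Late entry would count time after death as time without care, an error in the opposite direction.

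**Conclusion.** The concern holds as a structural bias of modest size. For undated decedents the observation time depends on the outcome, and the planned analyses neither correct nor test this. Where contact truly falls, the rule tends to understate the fall.

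For the whole cohort at about 1.5% yearly mortality, the shift in the rate ratio (about 0.002 or less) would not change any conclusion. At 10% mortality with every death undated it reaches about 0.015. Proportion indicators in high-mortality groups are the real exposure: a gain of under 1 point at 10% undated, about 3 at 50% and about 7 at 100% in the scenario shown. These figures rest on the assumed mortality, contact rates and share losing all contact, and on contacts being unrelated to approaching death. If few deaths lack a date, the point is minor; the article does not allow that to be judged. The documents do not support saying that the rule masks the pandemic effect overall.

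**What to change.** 1. Report the number of deaths without a recorded date, by period and by condition. This alone shows whether the issue is material.
2. Add a sensitivity analysis of the main outcomes in which undated deaths are not dated from the last contact. Where extraction history exists, place the death between the last extraction without deceased status and the first with it.
3. Where it does not exist, bound the result: date the deaths at the last contact in one run and at the end of available data in the other. Also show results with undated decedents excluded from both periods.
4. State what counts as a contact for the death rule, and how decedents enter the denominators of the 6- and 12-month proportions.

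The cost is one derived date and one additional set of runs on data already held. The drawback is that late entry of deceased status can turn time after death into apparent time without care, and that exclusion drops the very patients at issue. It should therefore be a bounding analysis beside the existing rule, not a replacement for it.

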### Variables of Interest

#### Primary Exposure

The primary exposure is the start of the pandemic in March 13, 2020. This date was selected as it marks the beginning of Canadian provincial governments responding to the formal declaration of the pandemic by the World Health Organization on March 11, 2020, by enforcing sweeping public health and safety measures. The prepandemic time frame used is defined as June 22, 2018, through March 12, 2020. The pandemic time frame used in this study runs from March 13, 2020, through December 31, 2022. In addition to comparison between these 2 periods, 30-day interval rates will also be calculated for selected outcomes and indicators where possible.

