**Methods:**

This is a retrospective, single-arm, pre-post study using Canadian Primary Care Sentinel Surveillance Network (CPCSSN) data. CPCSSN is a research network supported by a primary care electronic medical record database, comprising over 1500 physicians and nearly 2 million patients. We are examining changes in care (eg, frequency of contacts, laboratory tests and investigations, referrals, medications prescribed, etc) among adults. We will also examine indicators specific to evidence-based recommendations for care in patients with diabetes and those with heart failure. We will compare rates of outcomes during key periods of the pandemic between March 13, 2020, and December 31, 2022, with equal time periods before the pandemic. Differences will be examined among specific subgroups of adults, including by decade of age, number of comorbidities, and socioeconomic status. Regression models appropriate to outcome distributions will be used to estimate changes, adjusting for potential confounders. This analysis is part of a mixed-methods study with a qualitative component investigating how patients with diabetes with or without concurrent heart failure perceived the impact of the pandemic on access to primary care and health care–related decisions. This study was approved by the Hamilton Integrated Research Ethics Board (14782-C).

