#### Analyses of Changes Over Time

We will present the proportions of patients experiencing the outcomes for each time period or mean changes for continuous variables and 95% CIs. Statistical significance of changes from pre to post time period will be assessed using the McNemar test for binary variables, the Wilcoxon signed rank test for original variables, and the paired *t* test for continuous variables. Regression models appropriate to outcome distributions will be used to control for potential confounders of age (<70 vs ≥70 years), sex, count of comorbidities (CPCSSN-validated conditions), neighborhood income quintile, and CPCSSN network (corresponding to location within Canada). Interactions will be examined in the descriptive analysis and will be considered for inclusion in models if they are found to be relevant. We will present adjusted estimates and 95% CIs for outcomes and parameter estimates for the independent variable and covariates. Analyses will be completed using SAS (version 9.4; SAS Institute, Inc).

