### Future Analyses

We will attempt to extend our analyses to include the first half of 2022 when data become available if our timelines and resources allow. At the time of writing this protocol (May 2023), data were available up to December 2021. The additional 2022 data will allow us to investigate changes in primary care in the later portion of the COVID-19 pandemic, capturing the Omicron wave, and measure whether any changes identified in the earlier portion of the pandemic were sustained or returned to prepandemic patterns of care.

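### The prepandemic window (630 days) and the pandemic window (1,024 days as dated) are unequal and seasonally mismatched, against the abstract's promise of equal periods and with an end date the article itself contradicts

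*Protocol article*

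**What the plan says.** The Primary Exposure section fixes both windows: "The prepandemic time frame used is defined as June 22, 2018, through March 12, 2020", and "The pandemic time frame used in this study runs from March 13, 2020, through December 31, 2022". It then plans a direct contrast, with finer rates as an addition: "In addition to comparison between these 2 periods, 30-day interval rates will also be calculated for selected outcomes and indicators where possible".

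The abstract (Methods) describes the contrast differently: "We will compare rates of outcomes during key periods of the pandemic between March 13, 2020, and December 31, 2022", to be set against prepandemic experience "with equal time periods before the pandemic".

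Study Design bounds the extract: "Patient-level data extracted from the CPCSSN repository between 2018 and 2022 will be used". Future Analyses reports that data reached December 2021 at the time of writing and continues: "We will attempt to extend our analyses to include the first half of 2022", subject to timelines and resources.

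On analysis, the section Analyses of Changes Over Time says: "We will present the proportions of patients experiencing the outcomes for each time period". It names McNemar, Wilcoxon signed rank and paired t tests. The listed adjustment variables are age, sex, comorbidity count, income quintile and network.

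**The concern.** Three statements about the same contrast do not agree. The abstract says equal lengths, the Primary Exposure dates give unequal lengths, and Future Analyses gives a different end date.

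This matters because several indicators in Table 1 carry no time denominator: overall encounters (the only access measure), investigations, referrals, the number of patients with a given test, influenza vaccination and nicotine replacement prescriptions. Compared between windows of different length, such outcomes rise in the longer window with no change in care. The study is looking for reductions in care, so an artificial rise in the pandemic period would hide them.

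The windows also cover different parts of the year. That can affect even a properly computed rate, and no listed covariate addresses it.

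**Working it through.** **The article's own figures.** It gives no day counts for the windows. Its only computed figures are the paired sample sizes, 1276 (correlation 0.2) and 1432 (correlation 0.1), for a change from 50% to 55%. The McNemar formula n = (z_a√ψ + z_b√(ψ − d²))²/d², with d = 0.05, ψ = 0.4005 or 0.4503, and two-sided 5% and 80% power (both assumed), gives 1256 and 1412. With continuity correction it gives 1275 and 1432. The sample size reproduces and is not at fault. Its 5-point change serves below only as a yardstick.

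**Window lengths, both end days counted.**
- Prepandemic, June 22, 2018 to March 12, 2020: 193 + 365 + 72 = 630 days, which is exactly 21 intervals of 30 days.
- Pandemic to December 31, 2021: 294 + 365 = 659 days.
- Pandemic to June 30, 2022: 659 + 181 = 840 days.
- Pandemic to December 31, 2022: 659 + 365 = 1,024 days.

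**Can the windows be made equal with the stated end date?** A 1,024-day prepandemic window would start on May 24, 2017. The extract starts in 2018, which allows at most 365 + 365 + 72 = 802 prepandemic days. So no. Conversely, 630 days from March 13, 2020 end on December 2, 2021.

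**Length effect with no change in care.** Inputs: full follow-up, a constant event rate, and an assumed 50% of patients with at least one event in 630 days (the article gives no event rates). With L the pandemic length, counts scale by L/630, and the any-event proportion becomes 1 − (1 − 0.5)^(L/630).

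| Data end | L | L/630 | Counts | 50% becomes |
|---|---|---|---|---|
| Dec 31, 2021 | 659 | 1.046 | +4.6% | 51.6% |
| Jun 30, 2022 | 840 | 1.333 | +33% | 60.3% |
| Dec 31, 2022 | 1,024 | 1.625 | +62.5% | 67.6% |

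At 1,024 days, a starting proportion of 10% becomes 15.7%, 30% becomes 44.0%, and 70% becomes 85.9%.

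Sensitivity to between-patient differences, with a gamma-distributed rate of shape k: P = 1 − (1 + m/k)^(−k), where m is set to give 50% in 630 days and is then multiplied by 1.625. At 1,024 days this gives 61.9% (k = 1) and 58.8% (k = 0.5).

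**Seasonal mix.** March 13 to June 21 is 101 days and occurs once in the prepandemic window.

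| Window | March 13 to June 21 | October to March |
|---|---|---|
| Prepandemic, 630 days | 101/630 = 16.0% | 346/630 = 54.9% |
| Pandemic, 659 days | 202/659 = 30.7% | 293/659 = 44.5% |
| Pandemic, 840 days | 303/840 = 36.1% | 383/840 = 45.6% |
| Pandemic, 1,024 days | 303/1,024 = 29.6% | 475/1,024 = 46.4% |

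Full October to December quarters number 2 in the prepandemic window, 2 in the 659- and 840-day windows, and 3 in the 1,024-day window.

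**Equal length alone.** Cutting the pandemic window to 630 days (to December 2, 2021) removes the length effect, but October to March is then 41.9% against 54.9%. Calendar dates have to match as well.

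**The case against.** The strongest reply is that the large figures depend on an end date the study may never reach. With data to December 2021 the length effect is small: 4.6% on counts, 1.6 points on a 50% proportion, and the same number of autumn quarters for influenza vaccination. This stands, and it is why the size has to be given as a range. It does not settle the matter, because December 31, 2022 is still the date the Primary Exposure section fixes.

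Second, the abstract speaks of rates, Table 1 includes indicators per patient per year or over the last 12 months, and 30-day rates are planned. Indicators of that kind do escape the length effect. But the 30-day rates cover only selected outcomes and come on top of the two-period contrast, and several indicators remain plain counts or ever-in-period proportions.

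Third, an offset or a season term is a detail an article may leave to an analysis plan. That is fair, and their absence is not the finding. The finding is that the stated dates contradict the stated equality and the stated data availability.

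Fourth, the abstract may mean that each key pandemic phase is matched to its own equal prepandemic period. The article defines no such phases, and the contrast it does define is between the two unequal windows.

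A reader might also infer that the six-month indicators fall mechanically because a longer window holds more half-years to satisfy. That needs the criterion to hold in every half-year of the whole window. The wording fits a proportion per six-month interval equally well, and that has no length effect.

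**Conclusion.** The point holds. The defined contrast is 630 against 1,024 days, contrary to the abstract, and its end date conflicts with Future Analyses. For counts without a time denominator and ever-in-period proportions, the shift under no change in care ranges from 4.6% to 62.5% in counts, and from 1.6 to 17.6 points on a 50% proportion, depending on where the data end. With strong between-patient heterogeneity the 1,024-day shift is 8.8 to 11.9 points.

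These sizes rest on assumed event rates and full follow-up. Patients contribute only up to death, so the true inflation of counts would be somewhat lower. A reader might infer that the artefact is always several times the 5-point change used for sizing. The documents do not support that: the shift is below 5 points if data end in December 2021, and at 1,024 days it is 5.7 points from a 10% start.

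The seasonal mismatch is present under all three end dates. Its effect on outcomes cannot be sized, because the article gives no seasonal rates. That the 630-day window was built for an earlier end date is a plausible inference from the 30-day multiple, but the article does not say so.

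**What to change.** Reconcile the abstract, Primary Exposure and Future Analyses so that one end date and one statement on window length apply throughout.

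Make the main comparison equal in length and matched on calendar dates. One option is March 13, 2018 to December 31, 2019 against March 13, 2020 to December 31, 2021: 659 days each, with identical seasonal shares. It lies within the extract and the data reported as available, provided the extract is confirmed complete to December 31, 2021. Evaluate the 6- and 12-month indicators in matched intervals within these windows, and say that the criterion applies per interval.

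Report any 2022 data as a labelled extension, using calendar-matched windows or person-time rates with a season term. Person-time rates with a season term would also be a sound alternative for the main comparison.

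The cost is protocol wording and re-cutting windows in data already held; the main comparison needs no new extraction. The downside is that January 1 to March 12, 2020 (72 days) drops out of the main prepandemic window, and 2022 is covered only by the extension.

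### Methods specify inference only for a two-window pre-post contrast, although the Abstract promises key-period comparisons and the aims concern pandemic phases and recovery

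*Protocol article*

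**What the plan says.** **Windows.** Under Primary Exposure: "The prepandemic time frame used is defined as June 22, 2018, through March 12, 2020" and "The pandemic time frame used in this study runs from March 13, 2020, through December 31, 2022". The same section adds: "In addition to comparison between these 2 periods, 30-day interval rates will also be calculated for selected outcomes and indicators where possible". It attaches no model or test to those rates.

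**Inference.** Under Analyses of Changes Over Time: "Statistical significance of changes from pre to post time period will be assessed", by McNemar, Wilcoxon signed rank or paired *t* test. Regression models are to adjust for age (under 70 versus 70 and over), sex, comorbidity count, neighborhood income quintile and network. Calendar time, season and pandemic phase are not on the list.

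**Aims.** Study Design announces changes "before, and through the phases of, the pandemic". Future Analyses says that additional 2022 data would allow the study to "measure whether any changes identified in the earlier portion of the pandemic were sustained or returned to prepandemic patterns of care"; obtaining those data depends on timelines and resources. The Abstract says that key periods of the pandemic will be compared with prepandemic periods of equal length. The Methods neither date key periods nor name an analysis for them.

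**The concern.** The design has a single group and no comparator, so whatever changed between the windows for other reasons is read as the effect of the pandemic. A two-window average also mixes the first disruption with whatever followed.

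Three readings then cannot be told apart: a brief fall with full recovery, a small lasting deficit, and a drift that began before March 2020. The Introduction asks whether, and for whom, chronic disease care needs catching up, and that depends on which reading is true. With 875,934 patients, precision gives no protection, because small drifts will be statistically significant. The results are meant for policy and practice audiences (Dissemination).

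**Working it through.** **1. The plan's own figure.** Statistical Analysis and Power gives 1276 pairs (correlation 0.2) or 1432 (correlation 0.1) for a change from 50% to 55%. Alpha and power are not stated; two-sided 0.05 and 80% are assumed here.

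- Discordant share D = p1 + p2 − 2·p11, with p11 = p1·p2 + r·√(p1q1p2q2). For r = 0.2, p11 = 0.275 + 0.2 × 0.2487 = 0.3247 and D = 0.4005. For r = 0.1, D = 0.4503.
- n = (1.96·√D + 0.8416·√(D − d²))²/d², with d = 0.05, plus a continuity term 1/d = 20. This gives 1256 + 20 = 1276 and 1412 + 20 = 1432.

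Both figures reproduce exactly, so the sample size also rests on one paired pre-post contrast.

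**2. Length of the windows.** June 22, 2018, to March 12, 2020, is 630 days, or 21 thirty-day intervals. March 13, 2020, to December 31, 2022, is 1,024 days (34.1 intervals), and 1,024/630 = 1.63. Future Analyses says that at the time of writing "data were available up to December 2021". To December 31, 2021, the pandemic window is 659 days (22.0 intervals).

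**3. Season mix.**

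| Months | Pre | Post, to Dec 2022 | Post, to Dec 2021 |
|---|---|---|---|
| Dec–Feb | 181/630 = 28.7% | 211/1,024 = 20.6% | 121/659 = 18.4% |
| Mar–May | 104/630 = 16.5% | 264/1,024 = 25.8% | 172/659 = 26.1% |

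**4. What a prior trend would look like.** Distance between window midpoints = half the sum of the lengths.

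- To December 2022: (630 + 1,024)/2 = 827 days = 2.26 years. An assumed 2% per year gives 4.5%.
- To December 2021: (630 + 659)/2 = 644.5 days = 1.76 years, giving 3.5%.

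**5. Shapes that the contrast cannot separate.** These are illustrations with assumed values: noise-free 30-day rates, baseline 100, 21 intervals before and 34 after (22 after, to December 2021, in brackets).

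- Fall of 40% for 4 intervals, then full recovery: pooled change −40 × 4/34 = −4.7% [−7.3%].
- Constant small deficit: set to the same −4.7% [−7.3%]. Phase terms give −40, 0, 0 for the first shape and −4.7 throughout for this one [−7.3].
- No pandemic effect, prior decline of 0.25 per interval (about 3 per year): the prepandemic mean is 97.5 and the difference in means is 0.25 × 27.5 = 6.875, so the pooled change is −7.1% [−5.5%]. A segmented model returns zero level and slope change.
- Prior rise of 0.25 per interval with a true step of −6.9 [−5.4]: pooled change 0.0%. The segmented model recovers the step.

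The choice of model matters. A single level-and-slope break fitted to the first shape gives a level change of −16.8 and a slope change of 0.73 per interval, which describes neither the fall nor the recovery.

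**6. Precision.** With n = 875,934 and D = 0.4, the detectable paired difference is (1.96 + 0.84) × √(0.4/875,934) = 0.0019, or 0.19 percentage points.

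**The case against.** A reader might infer that no comparison by phase is planned at all. The documents do not support that: the Abstract promises key-period comparisons and Study Design speaks of phases. The supportable statement is that the Abstract and the Methods are not aligned. Even those comparisons, if carried out, would not remove a prior trend.

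A condensed article may leave model details to an analysis plan that is not shown, and it does not say that the 30-day rates will go unmodelled. That is fair for phase dates and model form. It does not cover the significance testing, which the article itself fixes as pre to post.

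A reader might also infer that a sharp fall followed by recovery would look unchanged. That needs an overshoot. A fall of 40% for 90 days and 10% for 270 days averages (−3,600 − 2,700)/1,024 = −6.2% with plain recovery. It shrinks to −2.9% only if a +5% overshoot lasts the remaining 664 days. On 659 days, with the overshoot for the remaining 299, it is −7.3%. In a cohort of this size none of these would pass as no change; what is lost is their interpretation.

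Nor is it right that the covariates capture nothing of cohort ageing. Age and comorbidity count bear on it, although age is coarse and updating over time is not stated. Trend and season are what the list lacks.

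Finally, the pooled contrast is a legitimate measure of net change and bears on catching up, and the recovery aim is conditional on 2022 data. Both points stand.

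**Conclusion.** The point holds as a mismatch between aims and inference. The only inference that the Methods specify is a contrast of two unequal, seasonally unlike windows, with no calendar-time, season or phase term. It cannot support statements about phases, about recovery, or about attribution to the pandemic rather than to prior trend.

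The trend distortion of 3.5% to 4.5% rests on an assumed 2% per year and on whether data end in December 2021 or December 2022. The documents give no prepandemic trend for any indicator, so the real size is unknown. The shapes in step 5 show ambiguity and do not predict results.

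The 30-day series cannot repair everything. It is planned only for selected outcomes, and indicators defined over 6 or 12 months do not form a simple 30-day series.

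**What to change.** 1. Date the key periods in advance and compare each with a season-matched prepandemic period of equal length, so that Abstract and Methods agree.
2. Name the outcomes that form a 30-day series. For these, prespecify a regression with a prepandemic trend, seasonal terms and allowance for autocorrelation. Use either a level-and-slope change or phase terms, without stacking redundant terms. Include an Omicron term only if 2022 data are obtained.
3. Base claims about phases, recovery and pandemic attribution on that model. Keep the pooled contrast as a description of net change.
4. For indicators defined over 6 or 12 months, use matched 12-month windows.
5. State a limit that the model does not remove: patients enter by having a contact between March 2018 and March 2020 (Study Population), largely inside the prepandemic window. Contact may fall afterwards through selection alone, and that fall could load onto the estimated change.

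The cost is modest modelling on a series already planned, with no new data source; at the time of writing only exploratory analyses had begun. The downside is imprecision: 21 prepandemic intervals cover less than two seasonal cycles, so trend and season will be estimated loosely and confidence intervals will be wider.
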